## Abstract

**Background::**

Total knee arthroplasty (TKA) has become the most preferred procedure by patients for the relief of pain caused by knee osteoarthritis. TKA patients aim a speedy recovery after the surgery. Joint mobilization techniques for rehabilitation have been widely used to relieve pain and improve joint mobility. However, relevant randomized controlled trials showing the curative effect of these techniques remain lacking to date. Accordingly, this study aims to investigate whether joint mobilization techniques are valid for primary TKA.

**Methods/Design::**

We will manage a single-blind, prospective, randomized, controlled trial of 120 patients with unilateral TKA. Patients will be randomized into an intervention group, a physical modality therapy group, and a usual care group. The intervention group will undergo joint mobilization manipulation treatment once a day and regular training twice a day for a month. The physical modality therapy group will undergo physical therapy once a day and regular training twice a day for a month. The usual care group will perform regular training twice a day for a month. Primary outcome measures will be based on the visual analog scale, the knee joint Hospital for Special Surgery score, range of motion, surrounded degree, and adverse effect. Secondary indicators will include manual muscle testing, 36-Item Short Form Health Survey, Berg Balance Scale function evaluation, Pittsburgh Sleep Quality Index, proprioception, and muscle morphology. We will direct intention-to-treat analysis if a subject withdraws from the trial.

**Discussion::**

The important features of this trial for joint mobilization techniques in primary TKA are randomization procedures, single-blind, large sample size, and standardized protocol. This study aims to investigate whether joint mobilization techniques are effective for early TKA patients. The result of this study may serve as a guide for TKA patients, medical personnel, and healthcare decision makers.

**Trial registration::**

It has been registered at http://www.chictr.org.cn/showproj.aspx?proj=15262 (Identifier:ChiCTR-IOR-16009192), Registered 11 September 2016. We also could provide the correct URL of the online registry in the WHO Trial Registration. http://apps.who.int/trialsearch/Trial2.aspx?TrialID=ChiCTR-IOR-16009192

## Background

1

Knee osteoarthritis (OA) is an ordinary degenerative joint disease and a primary cause of dysfunction in the elderly, thereby burdening health resources.^[1,2]^ Total knee arthroplasty (TKA) is recommended to ease the pain and increase the joint function of end-stage knee OA patients. The number of TKA patients in developed countries has increased sharply.^[3–5]^ Statistics show that 93% of knee OA patients experience relieved joint pain, alleviated stiffness, and improved movability after replacement.^[6]^ However, TKA often leaves early postoperative complications, such as pain, restricted joint activities, and muscle atrophy, which cause difficulty in daily life activities and reduce quality of life.^[7,8]^ Physical therapy can hasten the recovery of TKA surgery patients.^[9]^ In the United States, the latest research data show that the mean total TKA-related expenses are US $ 30,831; speeding up the recovery process can lessen TKA-related expenses.^[10]^

Traditional rehabilitation programs^[11]^ primarily aim to improve the knee strength, increase the range of movement, and enhance the gait of TKA patients. Early-stage TKA patients mainly lie in bed to perform straight leg-raising to increase quadriceps muscle strength and active joints.^[12]^ Even TKA patients who completed the traditional rehabilitation training plan still experience reduced walking speed and difficulty in climbing.^[13]^ The persistence of functional limitations signifies the need to find effective rehabilitation strategies for TKA surgery patients.

Joint mobilization techniques for rehabilitation are commonly employed by physical therapists to relieve pain and increase motion in TKA patients.^[14,15]^ Two reasons explain why joint mobilization techniques may be useful for primary TKA. First, early postoperative TKA is associated with pain and restricted range of motion.^[16]^ Joint mobilization may assist in reducing pain and increasing motion by passive oscillatory movements of small or large amplitude and sustained stretching.^[14]^ Second, TKA patients often encounter muscle weakness. Mobilization may accelerate TKA rehabilitation by increasing corticospinal excitability, allowing physiotherapists to optimize muscle recruitment rates and constant movement.^[17]^

A systematic review has shown that early mobilization after a hip or knee arthroplasty can reduce the length of hospital stay to about 1.8 days without any increase in adverse results.^[18]^ Joint mobilization, as a clinical commonly used intervention, can alleviate the chronic pain of knee OA patients by reducing the excitability of reflection.^[19]^ A further study on traction mobilization is important to revise TKA surgery such that the recovery of joint activities is promoted and the incidence of infection is managed.^[20]^ Many studies have reported the role of joint mobilization in the cervical vertebra, lumbar, shoulder, and ankle, but randomized controlled trials (RCTs) showing the effect of joint mobilization on early postoperative TKA rehabilitation remain lacking to date.^[21–23]^

Effective joint mobilization for primary TKA is important to promote the fast and efficient recovery of patients and to reduce economic expenditure. Hence, we project a single-blind RCT to conclude the effect of joint mobilization techniques for primary TKA.

## Methods/design

2

### Research object

2.1

We will accomplish an RCT on the effect of joint mobilization techniques for primary TKA to determine the following:1)Whether mobilization benefits the rehabilitation of primary TKA.2)Whether mobilization exerts better effects than physical modality therapy for primary TKA.3)The side effects associated with mobilization.

### Study method

2.2

We will design a single-blind RCT to compare the effects of joint mobilization techniques and physical modality therapy with usual care on TKA patients. A total of 120 patients with early postoperative TKA will be enrolled and investigated in Shanghai Shangti Orthropedic Hospital, Shanghai City, China.

All subjects will receive a questionnaire before the study. The questionnaire will include the following: basic information (eg, age), history of injury, pain (visual analog scale, VAS), knee function [the knee joint Hospital for Special Surgery (HSS) score], and Pittsburgh Sleep Quality Index (PSQI). All participants will sign a consent form before the study.

Subjects who meet the inclusion criteria divided into a 1:1:1 ratio will be randomly selected. After the random distribution, patients with early postoperative TKA will be distributed to a control group (regular training), a physical modality therapy group (physical therapy with regular training), and an intervention group (mobilization with regular training). The study period will last 6 months, including a 4-week intervention and follow-up of 2 to 6 months without intervention. Before intervention, evaluation will be conducted during the 2nd and 4th weeks and during the 3rd and 6th months.

### Participants

2.3

Inclusion criteria include the following:1.50 to 80 years old.2.With a diagnosis of knee osteoarthritis symptoms and surgical indications.3.Underwent first unilateral total knee replacement.4.With the same operation method, normal blood clotting index.5.Conscious and without cognitive impairment.6.Not more than 2 weeks after TKA.

Exclusion criteria include the following:1.With serious cardiovascular disease, neurological disease, osteoporosis and metabolic disease.2.Suffering from hemophilia, sever diabetes, tumor, or function of blood coagulation disorder.3.With fracture, dislocation, abnormal structure, and other surgeries.4.Inability to communicate in Chinese.

### Exit criteria and management

2.4

Early postoperative TKA patients will be allowed or be required to quit the study if1.Subject has a demand.2.Subject develops a serious disease (eg, heart disease).3.Subject experiences side effects with the treatment.

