### Measurement of outcomes

2.9

Tools to measure primary indicators include the following:1.The VAS is used to assess pain intensity. It has a length of 100 mm and a pain scale of 0 to 10, where 0 represents no pain and 10 represents unbearable pain. The pain intensity is determined by the patient.^[25]^2.The knee joint HSS score, with a 100-point scoring system, is used to gauge knee function. It applies the following criteria: pain, 30 points; function activity, 22 points; range of motion, 18 points; muscle strength, 10 points; flexion deformity, 10 points; and stability, 10 points. A score of ≥85 points is equivalent to best, 70–84 to good, 60–69 to medium, and ≤59 points to poor. The HSS score has become the gold standard to evaluate knee arthroplasty.^[26]^3.Adverse events associated with joint mobilization technique that will be recorded.

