### Statistical analysis

2.10

Statistical analyses will be implemented by SPSS 17.0 and Microsoft Excel 2007 software. Data will be represented as mean ± standard deviation (SD). We will use a 2-way repeated measurement analysis of diversification (group × time) to compute the impact of joint mobilization techniques, physical modality therapy, and the control process, which involve the preliminary and final intervention effects. If subjects fail to make a follow-up, we will use an intention-to-treat analysis. A *t*-test will be performed to compare the changes in measures within groups. Statistical significance will be considered at *P* < .05.

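### The exit rule takes patients with side effects or serious disease out of the study, not only off treatment, which conflicts with the safety objective and the intention-to-treat commitment

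*Protocol article*

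**What the plan says.** Exit criteria and management (2.4) lists three grounds on which patients are "allowed or be required to quit the study": the patient's own request, development of a serious disease, and "Subject experiences side effects with the treatment". The third ground has no severity threshold. What is left is the study; stopping the treatment alone is not mentioned, and no section says that evaluations go on after exit.

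Four other statements bear on this:

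- Research object (2.1) gives as its third aim "The side effects associated with mobilization".
- The Abstract counts adverse effects among the primary outcome measures, and Measurement of outcomes (2.9) lists among the primary indicators "Adverse events associated with joint mobilization technique that will be recorded".
- The Abstract states "We will direct intention-to-treat analysis if a subject withdraws from the trial", and Statistical analysis (2.10) states "If subjects fail to make a follow-up, we will use an intention-to-treat analysis".
- Study method (2.2) sets a 6-month study with 4 weeks of intervention and evaluations at weeks 2 and 4 and months 3 and 6.

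**The concern.** An intention-to-treat analysis depends on outcomes from everyone randomized, whether or not they stayed on treatment. Section 2.4 can end a patient's participation, against the patient's own wish, for an event that arises after randomization and may be caused by the treatment under test. This differs from ordinary dropout: the rule itself creates the missing data, and the reason is plausibly related to pain and function.

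Two things are at stake. First, the safety picture stops where it becomes interesting: the event is noted, but whether it resolves, persists or worsens is not. Second, if side effects lead to exit more often in one arm and those patients would have done worse, the observed means of that arm look better than they should. Mobilization and laser are each added daily to the regular training that all arms receive, so unequal exit is a reasonable expectation. The article documents no exit rate in any arm.

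**Working it through.** **The passages side by side**

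| Place | What it needs or causes |
|---|---|
| 2.4 | Exit from the study, optional or compulsory, on a side effect or serious disease |
| 2.1, third aim | Information on side effects of mobilization |
| 2.9 and Abstract | Adverse events as a primary outcome |
| 2.10 and Abstract | Intention-to-treat when patients withdraw or miss follow-up |
| 2.2 | Evaluations continuing to month 6 |

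A patient who has a side effect in week 1 and is made to leave contributes the event itself and the evaluation made before treatment. Weeks 2 and 4 and months 3 and 6 are lost. The first row therefore removes data that the other rows rely on.

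**Inputs from the article**

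- Total sample: "A total of 120 patients with early postoperative TKA will be enrolled".
- Allocation is 1:1:1, so 120 / 3 = 40 per arm.
- Significance level .05, with sidedness not stated; two-sided is assumed here.

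The article gives no SD, effect size, power, dropout rate or side-effect rate, so there is no plan figure to reproduce.

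**Assumed inputs, for illustration only**

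- Exit for side effects, mobilization arm (p_m): 5%, 10% or 20%, which is 2, 4 or 8 of 40 patients.
- Exit for side effects, usual care (p_c): 0% or 5%, which is 0 or 2 of 40.
- Deficit of leavers against stayers in later outcomes (g): 0.5 or 1.0 SD, the same in both arms.

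**Bias of the observed-data contrast**

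If stayers have mean m and leavers m − g, the full-arm mean is (1 − p)m + p(m − g) = m − pg. Observing only stayers therefore overstates the arm by pg. Between two arms the shift toward mobilization is g × (p_m − p_c).

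| p_m | p_c | g = 0.5 SD | g = 1.0 SD |
|---|---|---|---|
| 5% | 0% | 0.025 | 0.05 |
| 5% | 5% | 0 | 0 |
| 10% | 0% | 0.05 | 0.10 |
| 10% | 5% | 0.025 | 0.05 |
| 20% | 0% | 0.10 | 0.20 |
| 20% | 5% | 0.075 | 0.15 |

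**Yardstick**

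For two arms of 40, two-sided .05 and 80% power, the detectable difference is about (1.96 + 0.84) × √(2/40) = 2.80 × 0.2236 = 0.626 SD by the normal approximation and 0.634 SD by the t-test, so about 0.63 SD. The largest shift in the table is 0.20 / 0.63 = 32% of that, and the smallest is 0%. At 10% against 0% the shift is 0.05 to 0.10 SD, or 8% to 16%.

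**Lost power**

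At an assumed effect of 0.63 SD, power is 80.4% with 40 against 40, 78.3% with 36 against 40, and 75.7% with 32 against 40. The loss is small; bias is the more serious risk, because enlarging the sample does not remove it.

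**The case against.** The strongest reply is that this is a condensed article. It never says that data collection stops or that data are discarded at exit. It commits twice to intention-to-treat, and the handling of missing values may sit in an analysis plan that is not shown. All arms also do regular training, so side effects can occur under usual care too, and against the laser arm exits may partly cancel.

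Part of this stands. The missing-data method is not the finding. That later evaluations are lost is the plain consequence of leaving the study, not a rule spelled out in the text. The event that triggers exit can still be recorded, so the safety aim is weakened, not defeated.

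What does not stand is that intention-to-treat, or an unseen plan, cures the problem. Section 2.4 is a stated rule about leaving the study, not a silence. An analysis plan can choose how to impute, but it cannot restore observations that were never made.

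A reader might go further and infer that mobilization will look better the more side effects it causes. The article does not support that. It gives no exit rates, and the direction depends on conditions: exits more frequent under mobilization than in the comparator, later outcomes of leavers worse than those of stayers, and an analysis resting on observed data. With equal exits and equal deficits the shift is zero. With exits commoner under usual care, or leavers who would have done better, it reverses.

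**Conclusion.** The point holds as a conflict within the article. Section 2.4 ends study participation on a side effect of any severity or on serious disease, while the third aim, the primary adverse-event outcome and the intention-to-treat commitment all depend on continued observation. This rests on the wording alone and needs no assumed figure.

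The numerical consequence is not established. The 0 to 0.20 SD range rests wholly on the assumed exit rates and deficits, and its upper end requires a fifth of the mobilization arm to leave, none of the usual-care arm, and leavers a full SD worse. The 0.63 SD yardstick is for a simple two-sample comparison; the planned analysis is a group-by-time repeated-measures model, so it indicates scale only. Unequal exit is a reasonable expectation, not a documented fact. The text should be corrected because the possible bias is avoidable and cannot be fully repaired at analysis.

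**What to change.** Reconcile section 2.4 with the Abstract and sections 2.1, 2.9 and 2.10 by treating stopping of study treatment and leaving the study as two separate events. Whether and when treatment stops remains a clinical decision for the investigator; this review proposes no criterion for it. Then state that:

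- the planned evaluations at weeks 2 and 4 and months 3 and 6, and adverse-event follow-up, continue after treatment stops, wherever the patient is able and has not withdrawn consent;
- these patients are analysed in the arm to which they were randomized;
- the reason for and date of stopping treatment, and separately of leaving the study, are recorded.

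The cost is a change of wording in section 2.4, with matching wording in the consent form if it describes exit in the same way, plus some effort to keep in contact with patients who are off treatment. No evaluations are added to the existing schedule.

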### Interventions

2.5

Each group will finish usual training protocol twice a day for 4 weeks, and each section will receive health education before intervention. The subjects will be required to record the time and continuance of usual care protocol.

### Interventions group

2.6

All participants will undergo joint mobilization technical treatment facilitated by physical therapists. The first type of mobilization is the passive oscillatory movement, which is implemented in different ranges of motion or at the limit of the range. This procedure involves a sustained stretching with or without tiny amplitude oscillations for 30 s or more depending on the patient's feedback and desired effects. Accessory movement, shaft rotation, physiological movement, and combinations of any of these actions may form oscillations or sustained stretches. To eliminate any effect of mobilization, we will adopt joint mobilization in the Maitland level 4 grading method. For example, a tibiofemoral anteroposterior movement or patellofemoral movement may be performed to improve the knee flexion angle. This procedure will involve mobilization from grades I and II, followed by transition to grades III and IV, with every manipulation treatment taking 20 minutes at a time, once a day for 4 weeks.

### Physical modality group

2.7

The participants will undergo a semiconductor laser device (MDC diode laser system, MDC-1000-IBP) treatment. They will be treated with a laser dose of 6 J/cm^2^ over 8 points around the knee.^[24]^ The selected points are the surgical incision, medial and lateral femoral condyle, patellar up and down, and popliteal space. Laser therapy will be administered at a low power (50 mW, continuous wave, wavelength 880 nm) for 20 minutes at a time, once a day for 4 weeks.

### Control group

2.8

Participants in the control group will be subjected to regular training, including static quadriceps contraction, straight leg-raising, bridge, ankle pumps, knee joint active movement, and so on. Participants in the intervention group will undergo regular training with joint mobilization, whereas those in the physical modality group will undergo training similar to those in the control group but with physical factors. Regular training takes 20 minutes at a time, 2 times a day for 4 weeks.

### Measurement of outcomes

2.9

Tools to measure primary indicators include the following:1.The VAS is used to assess pain intensity. It has a length of 100 mm and a pain scale of 0 to 10, where 0 represents no pain and 10 represents unbearable pain. The pain intensity is determined by the patient.^[25]^2.The knee joint HSS score, with a 100-point scoring system, is used to gauge knee function. It applies the following criteria: pain, 30 points; function activity, 22 points; range of motion, 18 points; muscle strength, 10 points; flexion deformity, 10 points; and stability, 10 points. A score of ≥85 points is equivalent to best, 70–84 to good, 60–69 to medium, and ≤59 points to poor. The HSS score has become the gold standard to evaluate knee arthroplasty.^[26]^3.Adverse events associated with joint mobilization technique that will be recorded.

Tools to measure secondary indicators include the following:1.Manual muscle testing is used to evaluate the knee joint muscle strength.^[27]^ It does not require any equipment when performing strength evaluation of subjects. It applies the following ratings: 0 as zero (O), 1 as trace (T), 2 as poor (P), 3 as fair (F), 4 as good (G), and 5 as normal (N). This procedure evaluates the function and strength of individual muscles based on the effective performance of a movement in relation to the forces of gravity and resistance. This method is simple, easy, and has been widely used in clinics.2.Joint position matching test is used for knee proprioception.^[28]^ The subject will be asked to move to a reference position (flexion or extension) and maintain in this position for 3 seconds, and then repeat from the starting position to the reference position. The participant will determine the best position and will remain in this posture so that the assessor measures the position and angle. This test will be repeated three times, and the results will be averaged. Greater absolute error corresponds to worse proprioceptive.3.Berg balance scale has been diffusely used to test the patient's static and dynamic balance abilities. This tool evaluates standing up, sitting down, standing alone, closing one's eyes, raising arms forward, turning, and stepping on one's foot, for 14 times. The ratings of this type of scale are as follows: 0–20 points, balance ability is poor; 21–40, with medium fall risk; and 41–56, with low fall risk.^[29]^4.In muscle morphology, a musculoskeletal ultrasound is performed with the use of an ultrasonic machine to measure the thickness of the muscle around the knee joint.^[30]^5.Quality of life will be measured with the SF-36.^[31]^ The SF-36 simplified version includes physical activity and physical function with the role of self-evaluation of health, body pain, overall dynamic, social function, emotional impact on role function and mental health. SF-36 is recognized to be highly reliable in determining quality of life.6.PSQI^[32]^ scale is used to evaluate the quality of sleep of persons with mental disorders but can also be applied to persons with none. This measure consists of 19 self-evaluation and five other review items. It uses the scores 0–21 with 21 being the highest and implying a poor sleep quality.

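### The primary adverse-event outcome is defined by association with mobilization, which two of the three arms never receive, and this conflicts with the unrestricted wording in the Abstract

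*Protocol article*

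**What the plan says.** The article describes this outcome in three places.

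- Measurement of outcomes (2.9), under the lead-in "Tools to measure primary indicators include the following", gives as item 3: "Adverse events associated with joint mobilization technique that will be recorded".
- The Abstract (Methods/Design) ends its list of primary outcomes with "range of motion, surrounded degree, and adverse effect". Nothing there ties adverse effects to one treatment or one arm.
- Research object (2.1) states the third objective as "The side effects associated with mobilization".

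Two further passages bear on it. Exit criteria and management (2.4) lists, for any subject, "Subject experiences side effects with the treatment" as a reason to leave the study. Sections 2.7 and 2.8 set out what the comparators receive: laser plus regular training in one arm, and in the other regular training alone ("Participants in the control group will be subjected to regular training").

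**The concern.** An outcome defined by association with one arm's treatment cannot occur in the other arms. The definition in 2.9 would make two of the three arms structurally zero on a primary indicator.

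This matters because patients enter no more than two weeks after knee replacement, and the Background itself says that the operation often leaves pain, restricted movement and muscle atrophy early on. Some untoward events are therefore to be expected in every arm whatever the add-on treatment. Randomization offers a direct way to separate that background from any effect of mobilization, but only if events are counted by the same rule in each arm. Without that, every event in the mobilization arm has to be judged case by case. Background events may be charged to mobilization, or real harm may be put down to surgery, and there is no concurrent count to check either judgement. Events linked to laser or to the training itself would also fall outside the definition.

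**Working it through.** **Setting the text side by side**

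1. Section 2.9: an event counts if it is associated with mobilization.
2. Sections 2.7 and 2.8: the laser and control arms receive no mobilization. From 1 and 2, no event in those arms can meet the definition if it is applied as written.
3. Abstract: the outcome carries no restriction. An event in any arm can count.
4. Statements 1 and 3 define different outcomes. The article does not say which governs.
5. The third objective names no comparator. The second does: "Whether mobilization exerts better effects than physical modality therapy for primary TKA". So the third objective can still be answered by description. For example, 0 events in 40 mobilization patients would give a one-sided 95% upper bound of 1 − 0.05^(1/40) = 7.2% (two-sided 95% interval: 1 − 0.025^(1/40) = 8.8%). That bounds the rate of attributed events. It does not say how the rate compares with what happens without mobilization.

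**Illustration of what the literal definition could do**

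The article gives no adverse-event rate, so there is no figure of its own to reproduce. Inputs:

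- Patients per arm: 120 in a 1:1:1 ratio (2.2), so 120/3 = 40.
- Significance level: 0.05 (2.10), taken here as two-sided.
- Assumed: background rates of 5% to 20%, the same in every arm; every event in the mobilization arm attributed to mobilization; comparator fixed at 0/40; Fisher's exact test between two arms.

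Two-sided Fisher P for k/40 against 0/40 is 2 × C(40,k)/C(80,k):

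- k = 5: 2 × 658,008/24,040,016 = 0.055
- k = 6: 2 × 3,838,380/300,500,200 = 0.026

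Six events are therefore enough to reach P < 0.05. The chance of a false signal is P(X ≥ 6) with X ~ Binomial(40, p). For comparison, the last column gives the chance of P < 0.05 in either direction when both arms are counted by the same rule. It is obtained by summing the product of the two binomial probabilities over all significant tables.

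| Assumed rate p in every arm | Expected events, 40p | False signal, comparator fixed at 0/40 | Same rule in both arms |
|---|---|---|---|
| 5% | 2 | 1.4% | 0.4% |
| 10% | 4 | 21% | 1.7% |
| 15% | 6 | 57% | 2.5% |
| 20% | 8 | 84% | 2.8% |

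**The case against.** The best defence is that the article is loosely worded rather than deliberately restrictive. Section 2.9 does not contain the word only, and it does not say that other events go unrecorded. The Abstract is unrestricted. The exit criterion foresees side effects of treatment in any subject, so events in the comparator arms are at least contemplated. Collection forms and tabulation may well be in the full protocol or analysis plan, which are not shown. Some harm-related information is also captured in all arms by other outcomes: pain on the VAS and, if the Abstract's surrounded degree means limb circumference, swelling.

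Much of this stands. It shows that the documents do not establish that comparator events will go unrecorded. It does not remove the conflict. The exit criterion is a reason for leaving, not a recording rule, and is itself limited to effects put down to treatment. The outcome section is where a reader looks for the governing definition, and that definition is stated there, not left out.

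Three stronger readings are tempting but unsupported:

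- That the third objective cannot be judged at all. It is worded descriptively and can be described in the mobilization arm.
- That staff who know the allocation attribute the events. The article calls the trial single-blind but does not say who is blinded or who attributes events.
- That adverse events will be analysed by repeated-measures ANOVA or as means. Section 2.10 says in general that "Data will be represented as mean ± standard deviation (SD") but does not apply this, or any test, to adverse events.

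The illustration is also open to challenge. It depends on an assumed rate, on full attribution to mobilization and on a test the article does not plan. At a 5% rate the effect is small, and under-attribution would push the other way.

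**Conclusion.** The concern holds in this form: a primary outcome is defined in two incompatible ways, and the more detailed definition, if applied literally, cannot be met in two of the three arms. The randomized safety comparison would then be lost, and mobilization effects could not be separated from background postoperative events. Objective 3 would be reduced to a description of one arm of 40 patients.

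The size of the damage cannot be derived from the article. The false-signal figures, from 1.4% to 84% across assumed rates of 5% to 20%, show how strongly the result depends on a rate nobody has stated. They do not predict this trial's result, and the direction of error is not determined, since it depends on how events are attributed.

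**What to change.** Redefine the outcome in 2.9 as all adverse events, recorded by the same procedure at the same planned evaluations in all three arms, whatever the suspected cause. Make relatedness to the assigned treatment a separate field, so that events associated with mobilization can still be listed for the third objective. Report the number of patients with at least one event per arm, with risk differences and 95% confidence intervals. Bring the Abstract, 2.1 and 2.9 into line with that one definition.

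The cost is a change of wording and slightly more data entry in the comparator arms at evaluations already scheduled. It should be settled before data collection, because events not recorded in the comparator arms cannot be reliably recovered later. If the full protocol already collects events this way, only the article's wording needs correcting.

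### Adverse events are a primary indicator, but section 2.9 covers only those tied to mobilization and section 2.10 states no analysis that suits events

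*Protocol article*

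**What the plan says.** Three places in the protocol article give adverse events a leading role. The Abstract (Methods/Design) lists adverse effects among the primary outcome measures, without tying them to one arm. Section 2.1 makes the side effects of mobilization the third objective. Section 2.9 puts adverse events third among the primary indicators, in these words: "Adverse events associated with joint mobilization technique that will be recorded".

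Section 2.10 states the analysis in a few sentences. "Data will be represented as mean ± standard deviation (SD"), it says, with no restriction by outcome. It continues: "We will use a 2-way repeated measurement analysis of diversification (group × time"), then "A *t*-test will be performed to compare the changes in measures within groups", and "Statistical significance will be considered at *P* < .05". No outcome is named, and no method is given for event counts. Nor is one given for ordered grades, although section 2.9 scores manual muscle testing, a secondary indicator, on six steps from 0 that end in "4 as good (G), and 5 as normal (N").

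On size, section 2.2 says "A total of 120 patients with early postoperative TKA will be enrolled", allocated 1:1:1 to mobilization, laser (physical modality) and usual care.

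**The concern.** Two statements combine badly.

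- **Recording.** If only events linked to the mobilization technique are covered, patients in the other two arms can hardly contribute any, because they do not receive the technique. Pain, swelling and other problems in the weeks after knee replacement arise in every arm. Without uniform recording, the trial cannot separate what mobilization causes from what surgery and recovery cause.
- **Analysis.** A recorded event has no scale and no baseline value. A mean ± SD, a group-by-time model of means and a within-group change test do not give a risk per arm or a difference in risk.

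At stake are one of the primary indicators and the third objective. The recording half is the more urgent, because an analysis plan written later can replace a method but cannot restore events that were never collected.

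**Working it through.** The article gives no event rate, effect size or power for adverse events, so there is no stated figure to reproduce. The event counts and rates below are assumptions for illustration.

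**Inputs.** 120 patients, 1:1:1 (section 2.2): 120 / 3 = 40 per arm. Significance at 0.05 (section 2.10); sidedness is not stated and is taken as two-sided.

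**1. What one-arm recording does.** Assume the same background rate of 10% in every arm. The expected number is 0.10 × 40 = 4 patients per arm, so the true difference is zero. If the 4 in the mobilization arm are attributed to the technique and recorded, and the events in the other arms are not, the data read 4/40 v 0/40 v 0/40. With uniform recording, an arm with no events would have probability 0.9^40 = 0.015. At assumed rates of 5% and 2% the probabilities are 0.95^40 = 0.129 and 0.98^40 = 0.446.

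**2. What mean ± SD shows.** For an event indicator with rate p, the SD is √(p(1 − p)): 0.14 at 2%, 0.22 at 5%, 0.30 at 10%. The SD is at least three times the mean and adds nothing to p itself. With no events the summary is 0 ± 0. The exact two-sided 95% upper limit for 0/40 is 1 − 0.025^(1/40) = 0.088, or 8.8%.

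**3. Whether the choice of method matters.** Section 2.10 uses the t-test only within groups, so a two-sample t-test here stands in for a comparison of means of the ANOVA type.

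- 4/40 v 0/40, means: variance in the first arm (40/39) × 0.1 × 0.9 = 0.0923; pooled 0.0462; standard error √(0.0462 × 2/40) = 0.0480; t = 0.1 / 0.0480 = 2.08 on 78 degrees of freedom; p = 0.041.
- 4/40 v 0/40, Fisher: 2 × C(40,4)/C(80,4) = 2 × 91,390/1,581,580 = 0.116.
- 5/40 v 0/40, means: p = 0.021.
- 5/40 v 0/40, Fisher: 2 × C(40,5)/C(80,5) = 2 × 658,008/24,040,016 = 0.055.

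In both cases the two methods fall on opposite sides of 0.05.

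**4. Whether ANOVA inflates the error rate.** Simulated one-way ANOVA on an event indicator, three arms of 40 with equal rates, rejected in 3.0%, 3.8% and 4.4% of runs at assumed rates of 2%, 5% and 10%. That is at or below 5%. The disagreement in step 3 therefore shows that the conclusion depends on the method. It does not show that ANOVA is anti-conservative.

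**5. Muscle grades, for comparison.** Simulated between-arm tests at one visit, 40 per arm, assumed shares of 5%, 25% and 70% at grades 3, 4 and 5: type I error 4.9% (t) and 5.0% (rank); power at a common odds ratio of 3, 46.4% and 47.7%. With shares of 10%, 30% and 60%, power was 56.3% and 58.6%.

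**The case against.** The strongest reply is that this is a condensed article. Section 2.10 assigns no method to any named outcome, and for adverse events the text promises only that they will be recorded. Tests for safety data are commonly left to the full protocol or the analysis plan. Objective 3 can also be read as descriptive, with no promise of a comparison between arms.

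Much of this stands. A reader might infer that the article commits to ANOVA or mean ± SD for every outcome, adverse events included. It does not; that follows only from one unqualified sentence. The missing safety test, taken alone, is not a finding either.

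A reader might also infer that averaging the 0 to 5 muscle grades invalidates that comparison. The documents do not support this. It is a secondary outcome, and the simulated single-visit tests show almost no change in type I error and a power difference of 1.3 to 2.3 points. A mean plus SD above 5 is not an error, since an SD is not a range.

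A third tempting inference is that no events at all will be known from the other arms. Section 2.4 allows withdrawal for side effects of treatment without naming an arm, so some may surface that way, though not systematically.

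What the reply does not meet is the stated scope of the indicator. Section 2.9 positively limits it to events linked to one technique, while the Abstract carries no such limit. That concerns data collection, and a later analysis plan cannot repair it. Even a purely descriptive reading of objective 3 needs the background rate before an event can be called a side effect.

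**Conclusion.** The point holds for adverse events. As worded, a primary indicator has little or no comparator data, and the only analysis stated has no suitable form for it. The recording restriction carries most of the weight; the unrestricted analysis sentence is the lesser part and should be narrowed so that it does not appear to cover events.

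The size depends on event rates that the article does not give. At 40 per arm, no observed events would still be compatible with a true rate of up to 8.8%. An apparent 4 v 0 could come entirely from uneven recording if the background rate were about 10% and the mobilization-arm events were attributed to the technique. The verdict assumes that section 2.9 means what it says; if the full protocol already requires uniform recording, only the wording needs correction.

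The change will not make the trial powered for safety: even 5/40 v 0/40 gives p = 0.055 by Fisher's test. The intervals are therefore the main result. The muscle grades do not form part of the finding.

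**What to change.** - **Section 2.9:** record all adverse events in the same way, at the same visits and with the same questions, in all three arms, whatever their judged relation to the technique. Judged relatedness can be kept as a separate field. Align the Abstract and section 2.1 with this.
- **Section 2.10:** restrict mean ± SD, the group-by-time ANOVA and the t-test to the scored or continuous outcomes.
- **Section 2.10:** for adverse events, report the number of patients with at least one event in each arm, with exact 95% intervals. Give risk differences with Fisher's exact test for two named contrasts: mobilization v usual care, and mobilization v physical modality.
- **Optional:** show muscle strength as counts per grade beside the means.

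The cost is uniform event recording in two further arms at visits already planned, a few sentences in the protocol and a little more analysis. The recording change has to be in place before events are collected; the analysis change can follow in the analysis plan.
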